## Abstract

**Background:**

Aging has been associated with a progressive loss of skeletal muscle quality, quantity and strength, which may result in a condition known as sarcopenia, leading to a decline in physical performance, loss of independence and reduced quality of life. While the cause of impaired physical functioning observed in elderly populations appears to be multifactorial, recent evidence suggests that age-associated alterations in gut microbiota could be a contributing factor. The primary objective will be to assess the effects of a dietary synbiotic formulation on sarcopenia-related functional outcomes such as handgrip strength, gait speed and physical performance within older individuals living independently. The secondary objective will be to examine associations between changes in gut microbiota composition, functional performance and lean muscle mass.

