While the cause of age-related changes in muscle mass and physical functioning is likely multifactorial, recent evidence suggests that alteration in gut microbiota may play a role [9, 10]. It has been estimated that the human gastrointestinal tract (GIT) contains approximately 10^14^ microorganisms with more than 1000 distinct bacterial species [11]. While *Bacteroidetes*, *Firmicutes*, *Proteobacteria*, and *Actinobacteria* are the predominant bacterial phyla represented in the gut microbiota [12], each person (host) appears to have a unique biological relationship with its microbiota [13]. Analyzing fecal samples obtained from 728 older women, Jackson et al. found a negative association between host frailty and microbiota diversity [14]. The gut-muscle axis has received attention recently with suggestions that the composition and diversity of gut microbiota can be a determinant of skeletal muscle mass and metabolism [9]. Emerging evidence, predominantly in pre-clinical models, suggests disruption to the balance between microbial communities, such as depletion of symbionts and commensal bacteria and over-representation of opportunistic pathogens (such as those seen in gut dysbiosis), may contribute to the aforementioned age-related changes [9, 15, 16]. Indeed, with advancing age, where malnutrition, inactivity and chronic diseases are often experienced, gut dysbiosis is observed [17]. Conversely, individuals with successful aging, such as centenarians, demonstrate elevated representation of “good” bacteria, such as *Bifidobacteria* [18].

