#### Secondary aim

To determine the effect of a synbiotic formulation on muscle mass and architecture, microbiota composition and diversity and their associated metabolites, and self-reported indicators of sarcopenia.

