Wilcoxon’s signed-rank test, Spearman’s rank correlation (p), Pearson’s correlation (r), multiple linear regression, and/or linear mixed models will be used to examine associations and appropriate comparisons depending on the distributions of the variables. Relationships between markers of functional performance, ordinations of stool microbiota composition, and stool/plasma metabolites will also be assessed using the Structural Equation Model to enable causal assumptions to be interpreted between variables to ensure these relationships are not “coincidental” and linear mixed models. All mixed models will include the subject as a random factor and time as a continuous covariate. Backward stepwise regression will be used to identify the strongest predictors of changes in aspects of functional performance. The false discovery rate for all tests will be controlled by adjusting *P* values using the Benjamini–Hochberg procedure. Adjusted *P* values will be presented as *Q* values. Statistical analyses will be completed using SPSS v.26. 11.2.2

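### The secondary objective concerns associations between changes, but the association mixed models are not tied to within-person change, so a cross-sectional link could be read as linked change

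*Protocol article*

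**What the plan says.** The Abstract (Background) states: "The secondary objective will be to examine associations between changes in gut microbiota composition, functional performance and lean muscle mass". Under Objectives, the Secondary aim is different: "To determine the effect of a synbiotic formulation on muscle mass and architecture, microbiota composition and diversity and their associated metabolites". That is a treatment-effect aim and names no association between changes.

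The association methods are in Statistical analyses and power.
- A general sentence lists rank and product-moment correlation and adds that "multiple linear regression, and/or linear mixed models will be used to examine associations and appropriate comparisons depending on the distributions of the variables".
- A more specific sentence says "Relationships between markers of functional performance, ordinations of stool microbiota composition, and stool/plasma metabolites will also be assessed using the Structural Equation Model", and names linear mixed models as well.
- For the mixed models it adds: "All mixed models will include the subject as a random factor and time as a continuous covariate".
- A backward stepwise regression then looks for predictors of change in functional performance.
- P values are to be adjusted by Benjamini–Hochberg.

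Study assessments and the fecal microbiota section put performance testing and stool sampling at the same four visits (baseline and weeks 8, 16 and 20). DXA is done at baseline and week 16 only.

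**The concern.** The objective asks whether, when a person's microbiota changes, that person's function changes too. The variables listed for the mixed models are performance markers, microbiota ordinations and metabolites, with no mention of change. A subject random factor needs several rows per person, so the natural reading is that visit values enter the model.

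A random intercept accounts for correlated rows. It does not remove an association that lies between people. If people with better function have a different gut flora throughout, through age, diet or health, one slope on visit values picks that up. An arm term would not help, because this confounding exists within each arm. The protocol gives reason to expect such a link: its Background cites a study of 728 older women that "found a negative association between host frailty and microbiota diversity".

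At stake is a report that gut and muscle change together when the data show only that different people differ. The trial's repeated measurements could separate the two.

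**Working it through.** The protocol gives no figure for the association analyses, so there is nothing to reproduce. The check asks how far the stated structure, fitted to visit values, can mistake one association for the other.

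**Inputs from the protocol**
- Visits: T = 4 for both performance and stool.
- Outcome intraclass correlation: 0.7, taken from the pre/post correlation in the sample size paragraph.
- Sample size: 74 enrolled; with about 30% dropout, 74 × 0.7 = 51.8, or about 52.
- Significance level: 5% (sidedness is not stated; two-sided used).

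**Assumptions not in the protocol**
- Microbiota intraclass correlation: 0.5, 0.7 or 0.9.
- Correlation r of the two stable person-level values: 0, 0.3 or 0.5.
- True within-person association: zero.

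**Weights in the single slope** (unit variances, information per person)
- Between: T × var(person mean of x) / (σ²e + T × σ²u).
- Within: (T − 1) × σ²within,x / σ²e.

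With σ²u = 0.7 and σ²e = 0.3 for the outcome:

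| Microbiota ICC | Between | Within | Between share |
|---|---|---|---|
| 0.5 | 4 × 0.625 / 3.1 = 0.81 | 3 × 0.5 / 0.3 = 5.0 | 14% |
| 0.7 | 4 × 0.775 / 3.1 = 1.00 | 3 × 0.3 / 0.3 = 3.0 | 25% |
| 0.9 | 4 × 0.925 / 3.1 = 1.19 | 3 × 0.1 / 0.3 = 1.0 | 54% |

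**One cell by hand** (ICC 0.7, r = 0.3)
- Between-person slope: 0.3 × 0.7 / 0.775 = 0.271.
- Blended slope: 0.25 × 0.271 = 0.068, although the within-person slope is zero.
- n = 52: standard error 1/√(52 × 4.0) = 0.069, expected z about 0.98, rejection about 16%.
- n = 74: standard error 1/√(74 × 4.0) = 0.058, expected z about 1.17, rejection about 21%.

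**Simulation** (random-intercept model with linear time, 2000 runs per cell). Rejection rate of the single slope for microbiota ICC 0.5 / 0.7 / 0.9:

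| r | n = 52 | n = 74 |
|---|---|---|
| 0 | 5.3% / 5.6% / 5.5% | 6.6% / 5.4% / 5.2% |
| 0.3 | 10.4% / 16.8% / 35.6% | 13.5% / 23.8% / 46.6% |
| 0.5 | 22.1% / 42.8% / 81.4% | 30.0% / 55.4% / 91.6% |

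The hand calculation agrees closely. The mean spurious slope for r = 0.3 or 0.5 was 0.04 to 0.26 SD per SD.

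**Alternatives on the same data.** With the predictor split into person mean and visit deviation, the within-person test rejected in 4.3% to 5.9% of runs. The correlation of baseline-to-week-16 change scores rejected in 4.2% to 5.8%. Both hold the nominal 5%.

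**The case against.** The strongest reply is that the protocol does not commit to the faulty model. It says what the mixed models include. It does not say that raw levels are used, that there is one slope, or that the subject term is the only safeguard. Person-mean centring or change predictors would fit the same sentence, and such detail often sits in a full protocol or SAP that is not shown. This stands as a limit on the claim: a reader might infer that the plan relates levels using only a subject random factor, and the text does not support that. It does not remove the point. The article fixes a structure for all mixed models, and that structure does not by itself isolate the change that the Abstract asks about.

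Second, change is not wholly absent. The stepwise regression has change in performance as its outcome, and the listed correlations and regressions could use change scores. This also stands, but the stepwise predictors are not said to be changes, and the correlations and regressions are not said to use change scores.

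Third, a reader might infer that lean mass, named in the Abstract, has no association analysis because the list "Relationships between markers of functional performance, ordinations of stool microbiota composition, and stool/plasma metabolites" leaves it out. The documents do not support this. That list is introduced as additional, and the general sentence on associations restricts no variables.

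Fourth, the rates rest on two assumed quantities and on unadjusted tests. The Background gives no correlation coefficient, and the Discussion calls this kind of evidence inconclusive. Benjamini–Hochberg would lower the rates. It would not cure the bias, because it adjusts the P value of a slope that targets the wrong quantity.

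**Conclusion.** The point holds as a mismatch between objective and method: the association mixed models are not tied to within-person change, and neither the structural equation model nor the other listed methods is stated to close the gap. If the mixed models are fitted with one slope on visit values, a null within-person relation is rejected in about 10% to 81% of trials at n = 52. That range assumes an outcome intraclass correlation of 0.7, a microbiota intraclass correlation of 0.5 to 0.9, a person-level correlation of 0.3 to 0.5 and unadjusted 5% tests. With no person-level correlation there is no inflation.

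The consequence is confined to the secondary association objective. The primary outcomes and the between-arm comparisons are not affected. The change is worth making because it costs little and answers the stated objective directly.

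**What to change.** Before unblinding, add to the protocol or SAP:

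1. In every association mixed model, enter the microbiota or metabolite predictor as two terms: the participant's mean over visits and the visit's deviation from that mean. Take the within-person coefficient as the answer to the Abstract's secondary objective, and report the between-person coefficient as cross-sectional.
2. For DXA lean mass, which has two scans, relate the baseline-to-week-16 change to the microbiota change over the same interval.
3. Run simple correlations for this objective on change scores, not on pooled visits.

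The cost is two derived columns per predictor and a few lines of text, with no new data or visits. The downside is that within-person slopes are less precise and may look smaller than the blended ones.

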### Primary outcome measure: SPPB

Physical performance will be measured with the SPPB, which is a well-validated and widely used tool [36] that has excellent test–retest reliability and predictive validity [37, 38]. The SPPB measures three components (i) standing balance, (ii) 4-m habitual gait speed, and (iii) repeated chair rises. Each of the three domain scores ranges from 0 to 4 points, yielding a composite score ranging from 0 to 12 points. Higher scores indicate better function. A total score of fewer than 10 points indicates a high risk of frailty and falls [38] and a one-point change is considered clinically meaningful [39, 40]. SPPB component measures will be scored according to Table 1.

**Table 1 Tab1:** Scoring schema for SPPB

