### Primary outcome measure: handgrip strength

Handgrip strength will be measured using a Jamar analog hand dynamometer (Patterson Medical, Warrenville, IL) with the handle set to position II. Participants will be instructed to grip the device and squeeze as hard as possible with their dominant hand [49]. Three trials will be recorded with participants in a sitting position, elbow by their side and flexed at 90°, forearm and wrist in a neutral position, with shoulder adducted and neutrally rotated, as previously described [50]. The maximum of these values will be used for analyses [51]. Grip strength has been shown to predict future function [52] and has been negatively associated with frailty [53].

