### Primary outcome measure: TUG test

The TUG test measures the time (in seconds) taken to stand up from a standard chair, walk to and around a marker placed 3 m away at a comfortable pace, return to the chair and sit back down [54]. Participants will be permitted to use walking aids (if necessary) and will be instructed not to use their arms to stand up. Beginning with the participant seated with their back against the backrest of the chair, timing will commence on the command “go” and will stop when the participant returns fully seated in the back of the chair. The task will be performed twice, with the faster (shorter) time used in data analysis. TUG has been used to examine gait, agility, fall risk, balance, and dynamic (turning) movements in older adults [43, 55–57].

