### Hypotheses and study endpoints

#### Primary aims

We hypothesize 16 weeks of ingesting a synbiotic preparation compared to placebo will result in statistically significant improvements (within-group and between-group) in:4-m gait speedStanding balanceRepeated chair risesTimed up and go Handgrip strength

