### Statistical analyses and power

This estimated sample size for the main outcome measures of physical performance was based on an assumed correlation of 0.7 between the pre- and post-intervention outcome measures, and an effect size of Cohen’s *d* = 1.2 for gait speed based on data from Román et al. [29] that examined the effects of a multi-strain probiotic on gait speed and the TUG test in a study cohort of 35 (17 and 18 in treatment and placebo groups, respectively). To have a power of 80% and a significance level of 5%, our study aims to enrol an estimated sample size of 74 participants (37 per group), taking into account a conservative ~ 30% dropout rate.

The study hypotheses will be addressed using a hierarchical linear model analysis to test for significant differences between the two comparative groups (intervention and placebo) over time. A primary intention to treat (ITT) analysis will be conducted on all the participants who complete the trial. Additionally, a secondary analysis will be carried out to include only participants who consumed ≥ 90% of their supplement over the course of the intervention period. Between-group comparisons will be made using linear models and statistical significance set at *p* < 0.05. Where there are significant group xtime interactions, planned contrasts will compare changes from baseline under each intervention. Similar tests will be performed for the secondary hypotheses, using appropriate transformations if these measures exhibit non-normal distributions across time points. This analysis will allow for the control of any baseline group differences and to test for moderation effects in terms of these variables over time. Analysis of microbial community composition will be conducted using Phyloseq and vegan package in R version 3.6.1 as per protocol.

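### The primary outcomes are listed in two different ways, and the false discovery rate is controlled over all tests, so the bar for a primary claim depends on how many secondary tests are run

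*Protocol article*

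**What the plan says.** **Primary set.** Three section headings carry the primary label: "Primary outcome measure: SPPB", "Primary outcome measure: handgrip strength" and "Primary outcome measure: TUG test". The SPPB section describes three component scores "yielding a composite score ranging from 0 to 12 points". Under Hypotheses and study endpoints, Primary aims, the list is instead "4-m gait speedStanding balanceRepeated chair risesTimed up and go Handgrip strength" (run together in the extracted text). That is five variables, with no SPPB total, and improvement is expected both within and between groups. The Abstract speaks only of between-group change in physical performance to week 16. No section says whether any or all of the primary outcomes must be positive.

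**Sizing.** Statistical analyses and power bases the sample size on gait speed alone: d = 1.2, 80% power, 5% significance, 74 enrolled, about 30% dropout.

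**Error rule.** The same section states: "Between-group comparisons will be made using linear models and statistical significance set at" p < 0.05. Later it states: "The false discovery rate for all tests will be controlled by adjusting" P values with the Benjamini-Hochberg (BH) procedure, reported as Q values. It gives no family and no Q threshold. The paragraph with the BH sentence also covers correlations, structural equation models, stepwise regression, stool microbiota and metabolites.

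**The concern.** The SPPB total and its components are different variables. A total can move when no single component does, and the reverse. With two lists and no success rule, a reader cannot tell which result would count as a positive trial, and the choice could be made after the p-values are known.

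The error rule adds a second uncertainty. If the BH family really is every test, the hurdle for gait speed or handgrip is set partly by how many taxa and metabolites are tested and how many of them respond. Many null secondary tests make the hurdle much harder. Many responding secondary tests make it almost as loose as no correction. Neither should govern the trial's main claim.

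**Working it through.** **1. The two lists.**

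| Variable | Outcome headings | Primary aims |
|---|---|---|
| SPPB total (0 to 12) | yes | no |
| 4-m gait speed | only as SPPB component | yes |
| Standing balance | only as SPPB component | yes |
| Chair rises | only as SPPB component | yes |
| TUG | yes | yes |
| Handgrip | yes | yes |

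Both lists rest on the same physical tests. They differ on whether SPPB is analysed as a total or by component, and so on whether there are three or five primary tests.

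**2. The plan's own sample size.** On post scores, two-sided, n per arm = 2(1.96 + 0.84)²/1.2² = 10.9, so 11 (12 with the t distribution). After dropout, 12/0.7 = 17.1, so 18 per arm. The stated 37 is not reproduced. That is a separate matter. Here it means only that 37 × 0.7 = 25.9, or about 26 completers per arm, leaves ample power for gait speed tested alone. With noncentrality 1.2 × √(26/2) = 4.33 on 50 degrees of freedom, power is 98.9%.

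**3. BH over a pooled family, secondary tests null.** BH compares the k-th smallest p-value with 0.05 × k/m.
- m = 200: the threshold runs from 0.00025 (k = 1) to 0.00125 (k = 5).
- m = 1,000: it runs from 0.00005 to 0.00025.

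Simulated step-up power per primary, with five true primaries correlated 0.5, all other tests null and 26 per arm (a repeat run agreed within two percentage points):

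| Effect | Alone at 0.05 | 200 tests | 1,000 tests |
|---|---|---|---|
| d = 1.2 (stated) | 99% | about 78% | about 59% |
| d = 0.8 (assumed) | 81% | about 23% | about 11% |

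The test counts are assumptions; the article gives none. Taking power at the k = 5 threshold as a shortcut gives 81% and 65% at d = 1.2, and 31% and 17% at d = 0.8. That shortcut is too favourable, because it supposes that all five primaries are rejected every time.

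**4. BH over a pooled family, secondary tests responding.** If 100 secondary tests carry strong real effects (assumed) and all primaries are null, the chance of at least one false primary claim is about 14% for three primaries and 21% for five. The false discovery rate is held across the whole family, but the primary claim is not protected.

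**5. BH within the primary set alone.** Under a global null, the chance of any false claim is about 4 to 5% for three or five outcomes.

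**6. No correction, for comparison.** 1 − 0.95³ = 14% for three independent outcomes and 1 − 0.95⁵ = 23% for five. For five, simulation gives 18% at correlation 0.5 and 15% at 0.7.

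**7. Detectable effect at 80% power, 26 per arm, two-sided.** At alpha 0.05 it is 0.79 SD. At 0.05/5 = 0.01 it is 0.98 SD, or 0.98 × √(1 − 0.7²) = 0.98 × 0.714 = 0.70 SD with baseline adjustment at the plan's r = 0.7.

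**The case against.** Several points on the other side are sound.

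- **The two error statements need not conflict.** The ordinary reading is to adjust by BH and then judge at 0.05. A reader might infer that five primaries will be tested uncorrected, with a 23% chance of a false claim. The text does not support that, because it says all tests are adjusted. The figures in step 6 apply only if that sentence is ignored.
- **The lists do not name different tests.** The mismatch is total against components, which one sentence can settle.
- **Power is not wholly undefined.** A reader might infer that it is, but 80% is stated for gait speed at 5%. What is missing is power for the primary set and under BH.
- **At d = 1.2, correction within the primary set costs little.** Power for one outcome stays at about 96 to 99% under BH with three or five primaries. The serious loss needs pooling across many null tests, or a smaller effect than the plan assumes.
- **The pooled family is the literal reading, not a certain one.** Microbial composition is analysed in R and the statistical analyses are otherwise assigned to SPSS, which hints at separate families without saying so. Families are often set out in a SAP, and none is shown here. But the article does not merely leave the family open: it states one, all tests, and that statement is the problem.

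**Conclusion.** The point holds as an inconsistency in the primary set together with a badly fixed BH family. Even on the reading that reconciles p < 0.05 with BH, the primary threshold depends on the number and behaviour of secondary tests, and the chance of a false primary claim is not bounded.

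Under the null-secondary scenario, power per primary at the stated d = 1.2 drops from 99% to about 78% or 59%. Under the responding-secondary scenario, the chance of a false primary claim reaches about 14 to 21%. These figures rest on assumed test counts, 26 completers per arm, two-sided testing, d taken on the post-score scale and, for the power figures, a correlation of 0.5 among primaries. They show how the rule behaves and do not predict this trial's results.

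This should be fixed, but it does not invalidate the design. Nor do the documents require gait speed to become the sole primary outcome. It is the one the trial is sized on, but that choice belongs to the sponsor.

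**What to change.** 1. Use one primary list in the Abstract, the outcome headings and the Primary aims. State whether SPPB is analysed as a total or by component, and whether success means any, all or one named outcome.
2. Control error within that list alone, for example by Holm across it. If the sponsor prefers one primary outcome, name it and test it at 0.05; gait speed is the one used in the sample size.
3. Replace the all-tests BH sentence with separate BH families for the microbiome and metabolomic analyses, and state the Q threshold.
4. If five outcomes stay primary, restate the detectable effect at alpha 0.01: 0.98 SD unadjusted, 0.70 SD baseline-adjusted at r = 0.7.

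The cost is wording in the protocol or SAP and a registry update before unblinding. Either each primary outcome faces a somewhat stricter threshold than 0.05, or fewer outcomes carry the primary label. No extra participants or data are needed for this change.
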